**Null hypothesis: (H_0_: μ_1_=μ_2_)**		
	There is no time difference between using CAC^a^ and not using CAC for coding Swedish clinical notes	CAC does not affect a clinical coder’s coding quality
**Alternative hypothesis: (H_1_: μ_1_≠μ_2_)**		
	There is a significant time difference between using CAC and not using CAC for coding Swedish clinical notes	CAC affects a clinical coder’s coding quality by a significant margin

^a^CAC: computer-assisted clinical coding.

In additional exploratory analyses, we will examine the effect wrong suggestions have on the coder’s performance, and how often coders adopt these wrong suggestions. In addition, the distribution of the different professions between the groups as well as the coding experience will be explored.

To enable us to analyze the main outcomes in relation to text complexity, we distinguish between two categories of clinical texts: (1) short and simple texts (<512 tokens) and (2) long and complex texts (>512 tokens). However, we only consider the length of the text as the complexity dimension, as opposed to the complexity of the case or provided care, for example.

## Results

### Overview

Our results will be based on the statistical significance of the 2 tests related to time use and coding quality, which will allow us to conclude whether or not our CAC tool, the Easy-ICD, has the potential to impact clinical coding practice in a meaningful way. The expected results to be published summer 2024.

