### Sample Size Calculation

This experiment is novel, and we have not succeeded in finding many similar studies from which to estimate test parameters. Therefore, our experiment is important in that it provides baselines that may be useful for similar experiments in the future. We do expect a correlation between periods; the same coders are measured twice on mean performance in time, making a matched 2-tailed *t* test suitable for the task [26]. This matched 2-tailed *t* test (period) is done in 2 sequences, and the sample size calculation must therefore be doubled [27]. Further, each sequence will consist of approximately 10 coding instances, giving extra power to the estimation of the sequence mean. Due to the unknown nature of the expected effect size, the sample calculation in Figure 2 is made with 3 different effect estimates ranging in the upper level of medium to high effect. A pilot study is necessary to establish a probable effect size and adjust sample size estimation if needed.

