### Measurements and Analyses

The focus of our measurements is on how clinical coders perform with and without our system:

Compared with the performance of the unaided user, statistical tests of significance are used to check whether there are significant differences in the quality of coding when Easy-ICD is used, as measured by accuracy and *F*_1_-score.Time spent is the time it takes for a clinical coder to assign a code.System usability survey will be given to all participants to measure usability of the web interfaces, both with and without our Easy-ICD system.

Main analyses are based on hypothesis testing using the paired *t* test and Wilcoxon test to compare the before and after means at a significance level of .05. Table 1 summarizes these hypotheses based on a test of equivalence.

**Table 1 table1:** Time use and coding quality hypotheses testing to compare the before and after means.

Time use		Coding quality (accuracy and *F*_1_-score)

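### Significance against zero difference is used to decide whether Easy-ICD has meaningful potential; it can only show whether a difference was detected

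*Protocol article*

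**What the plan says.** The Overview under Results gives the rule for the main conclusion: "Our results will be based on the statistical significance of the 2 tests related to time use and coding quality". On that basis the authors will decide, yes or no, if the tool "has the potential to impact clinical coding practice in a meaningful way". This makes the rule two-way: it is meant to deliver a negative conclusion as well as a positive one.

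Measurements and Analyses specifies "hypothesis testing using the paired *t* test and Wilcoxon test to compare the before and after means at a significance level of .05". Table 1 sets a null of equal means against an alternative of unequal means for time use and for coding quality (accuracy and F1). It words the quality alternative as "CAC affects a clinical coder’s coding quality by a significant margin", without giving a margin. The text introduces the table with "Table 1 summarizes these hypotheses based on a test of equivalence", yet gives no equivalence margin either.

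Principal Findings, in the Discussion, combines the two outcomes. If one does not improve, the other must improve significantly, and slightly worse timing may be tolerated if performance is clearly better. No amounts are attached. The only numerical benchmark for any end point is the usability score of 68 in Evaluation Outcomes, which does not concern time or coding quality.

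**The concern.** A test of zero difference answers whether the data are compatible with no difference. It does not say whether the difference is large enough to matter to a coding service. It also does not show, when non-significant, that a worthwhile difference is absent. The article fixes a rule that uses the test for both purposes.

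The effective pass mark is then whatever observed difference reaches p<.05. That depends on how much coders vary and how many finish, and nobody has set it as a worthwhile amount. Recruitment is up to 30, and incomplete sessions are discarded, so the number analysed may be smaller. At stake is the headline conclusion: a tool with a useful effect could be written off, or a small detected effect presented as meaningful.

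**Working it through.** **Inputs from the article.** Paired t test, 2-tailed (Sample Size Calculation: "making a matched 2-tailed *t* test suitable for the task"), level .05, up to 30 participants in total.

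**Inputs not in the article.** It gives no SD of within-coder differences and no worthwhile difference. I assume an SD, s, of the within-coder difference in log time between 0.1 and 0.5, and show the range.

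**The plan's own figure.** The effect sizes behind the target of 30 appear only in Figure 2, which is not shown. A matched t test with an assumed standardised effect of 0.8 and assumed 80% power needs 15, and doubling for two sequences gives 30. This is consistent with the target but does not confirm it. The text says the planning effects were chosen because the effect is unknown, so they are not worthwhile amounts.

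**Pass mark in SD units.** The smallest observed difference that reaches p<.05 is t(0.975, n−1)/√n:
- n=30: 2.045/√30 = 0.373 SD
- n=20: 2.093/√20 = 0.468 SD

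**Pass mark as time saved.** Saving = 1 − exp(−0.373 × s) at n=30. The chance of significance comes from the noncentral t with standardised effect −ln(1 − saving)/s. For a true 15% saving and s=0.5 this effect is 0.1625/0.5 = 0.325.

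| Assumed s | Pass mark, n=30 | P(significant), true 5% saving | P(significant), true 15% saving | True 15% saving missed |
|---|---|---|---|---|
| 0.1 | 3.7% | 0.77 | 1.00 | <1% |
| 0.2 | 7.2% | 0.27 | 0.99 | 1% |
| 0.3 | 10.6% | 0.15 | 0.82 | 18% |
| 0.4 | 13.9% | 0.10 | 0.58 | 42% |
| 0.5 | 17.0% | 0.08 | 0.41 | 59% |

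At n=20 the pass mark runs from 4.6% (s=0.1) to 20.9% (s=0.5).

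**Coding quality.** With assumed SDs of the within-coder accuracy difference of 0.02, 0.05, 0.10 and 0.20, the pass mark at n=30 is 0.373 times each: 0.007, 0.019, 0.037 and 0.075.

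**What the interval adds.**
- s=0.5, n=30, observed saving 15%: log difference 0.163 ± 0.373 × 0.5 = 0.163 ± 0.187. The 95% CI runs from 2.4% longer to 29.5% saved. The test is non-significant and the rule gives a negative answer, yet the data are compatible with a large saving.
- s=0.1, n=30, observed saving 4%: 0.0408 ± 0.0373. The CI runs from 0.3% to 7.5% saved. The test is significant and the rule gives a positive answer; whether that saving matters depends on a value the article does not state.

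**The case against.** The strongest reply is that the article claims only potential, for a small and novel user study meant to provide baselines. Its Conclusions say that positive outcomes contribute to the evidence. Evaluation Outcomes and Principal Findings also make the favourable direction clear and weigh time against quality, so interpretation is not a bare two-sided p value. This stands as a limit on how strongly the point can be put. It does not remove the problem, because those passages attach no amount to any of their terms, and the Overview still rests a yes-or-no conclusion on the two tests.

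A reader might infer that the trial is likely to call a trivial saving meaningful. The documents do not support that. At n=30 significance needs an observed difference of at least 0.373 SD, and only s near 0.1 brings the pass mark below 4%. With 10 notes per period and no other source of variation, s=0.1 implies a per-note residual log SD of about 0.1/√(2/10) = 0.22. The two periods also use different notes, and any difference in difficulty would widen the paired spread. At s of 0.3 to 0.5 the pass mark is 10.6% to 17.0%, which is hard to call trivial.

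A pass mark that depends on SD and sample size is a property of any t test and is not itself a fault. Absence of confidence intervals or worthwhile values from a condensed article would not be a finding either, since a fuller plan may hold them. What remains is the rule that the article does state.

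**Conclusion.** The point holds in a limited form. The tests are usable as tests of difference. The error lies in the inference drawn from them: significance against zero cannot decide whether or not the tool has meaningful potential.

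Of the two possible errors, wrongly reading a non-significant result as no meaningful potential is at least as likely with 30 or fewer coders. A true 15% saving would be missed about 18% of the time at s=0.3 and about 59% at s=0.5. The opposite error, passing a saving of about 4%, needs s near 0.1. All of these figures assume 30 complete sessions and an SD that the documents do not give. Nothing here shows which error the trial will make.

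**What to change.** In the Overview under Results, replace the significance rule. Before analysis, the sponsor states a smallest worthwhile difference for time, for accuracy and for F1. The report then gives each within-coder difference with its 95% CI and words the conclusion as follows:
- a significant result supports the statement that a difference was detected;
- whether it is meaningful is judged from where the estimate and CI lie relative to the stated value;
- a CI that includes both zero and the stated value is reported as inconclusive, not as no potential.

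Requiring the CI bound itself to clear the stated value is optional and stricter. With s=0.3, n=30 and an illustrative 5% value, the observed log difference would have to reach 0.112 + 0.051 = 0.163, a saving of about 15%, so the claim may often be out of reach at this size. Rewording the quality alternative in Table 1 to say that the difference is not zero is editorial.

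The cost is three values agreed in advance and a changed paragraph, with no further participants or data. The downside is a more modest headline conclusion.

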### Evaluation Outcomes

The evaluation outcomes are as follows: (1) clinical coders aided by our Easy-ICD system are expected to yield better performance, that is, the accuracy and *F*_1_-score. (2) We expect that the Easy-ICD system will result in time savings during coding tasks. Looking at the 2 categories of clinical notes, it can be expected that the most time savings could be gained with large and complex texts. Such cases take more resources than shorter and simpler texts. (3) We expect the usability of the system to have a system usability score over the generally accepted normal score of 68 [29]. Further, we do not expect any significant differences between the usability of the user interfaces with and without our CAC system.

## Discussion

### Principal Findings

There are 2 primary areas of interpretation with which our study is concerned. The first relates to the quality or accuracy of clinical coding. If it shows that coders aided by our system perform better than unaided coders, we can conclude that our system is a useful tool to improve the quality of clinical coding. If, on the other hand, no significant improvement in accuracy is noted, we have to look to the other measurement point for complete interpretation. Time efficiency is the other interpretation point, where we would like to see significant time improvement between the intervention and control.

If the accuracy is not better, then the time savings must be significant. If there are no time savings, then the improvement in accuracy must be significant. It can also be argued that the CAC system is still useful even if the timing is slightly worse, while the performance is better by a significant margin.

If neither time nor accuracy improves, then we have to think about improving the system for future studies. Regardless, we plan to publish our findings in an international (or Nordic) peer-reviewed journal or conference and note all the facilitating factors and barriers.

In terms of usability, if there are no significant differences in usability scores, then usability issues can be ruled out. If the CAC system has significantly better usability scores, we expect the usability scores of the standard interface to be no worse than what is considered normal.

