### Specific Aims

The aim of the project is to investigate artificial intelligence tools, natural language processing specifically, to improve the quality of *ICD-10* coding. The goal of the user study is to test whether our Easy-ICD system can reduce the burden of coding and also improve the quality of *ICD-10* coding. The main end points to measure are (1) the individual’s coding accuracy averaged across all instances and *F*_1_-score (harmonic mean of recall and precision, each of which is averaged over all instances), (2) time use for assigning codes, and (3) usability based on the system usability scale [20].

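### The tool can be judged useful on either time or quality, from six p-values at .05 with no deciding measure or test, and the text does not say what a loss on the other endpoint would mean

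*Protocol article*

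**What the plan says.** Under Results, Overview, the protocol article states: "Our results will be based on the statistical significance of the 2 tests related to time use and coding quality". These are to decide whether the tool has the potential to affect coding practice.

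Principal Findings then describes how the two results combine. Better quality supports calling the system useful. Failing that: "If the accuracy is not better, then the time savings must be significant". The mirror case follows, with no time saving but a significant accuracy gain. It adds that one could argue that "the CAC system is still useful even if the timing is slightly worse, while the performance is better by a significant margin". Only the case where neither improves leads back to improving the system.

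Measurements and Analyses looks for "significant differences in the quality of coding when Easy-ICD is used, as measured by accuracy and *F*_1_-score", and bases the main analyses on the paired t "test and Wilcoxon test to compare the before and after means at a significance level of .05". Specific Aims lists "coding accuracy averaged across all instances and" F1 together as the first main end point, without ranking them. Table 1 states two-sided hypotheses, for example "There is a significant time difference between using CAC and not using CAC for coding Swedish clinical notes".

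**The concern.** An either/or criterion gives the tool two chances to succeed. Two quality measures and two tests per measure add more. The article fixes the .05 level and the either/or logic, but not which measure or test decides. An analyst facing a significant t test and a non-significant Wilcoxon, or a gain on F1 but not on accuracy, could justify either conclusion.

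The second gap is direction. Accuracy that is not better may be unchanged or worse, and the text treats the two alike. Slightly worse time is tolerated with no number attached. Table 1 is introduced as a test of equivalence, but its hypotheses are tests of difference without a margin, so it gives no protection. The stated goal is to reduce burden and also improve quality. A tool that speeds coders up by leading them to adopt wrong suggestions would not meet that goal, yet could be read as useful.

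**Working it through.** **Inputs from the article.** Two-sided .05 per test; paired t and Wilcoxon; time, accuracy and F1; up to 30 participants in total, from a matched t test doubled for two sequences. Usability is also a main end point but plays no part in the either/or reading, so it is left out.

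**Assumptions.** Normal paired differences; accuracy-F1 correlation 0.8 (range 0.7 to 0.9); time independent of quality (range -0.3 to 0.3). The article gives none of these.

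**1. The plan's own figure.** The effect sizes are in a figure that is not shown, so 30 cannot be reproduced outright. Paired t power uses a noncentral t with n - 1 degrees of freedom and noncentrality d√n. With an assumed d = 0.8 and n = 15, noncentrality is 0.8 × √15 = 3.10 and power is 82%. Fifteen is the smallest n reaching 80%, and 2 × 15 = 30. The stated total is consistent with that, for one test at 5%.

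**2. Count of tests.** 3 measures × 2 tests = 6 p-values, where the Overview counts 2.

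**3. False significance when the tool has no effect.** For k independent tests:
- any direction: 1 - 0.95^k, giving 0.0975 (k = 2) and 0.143 (k = 3);
- in the tool's favour: 1 - 0.975^k, giving 0.049 (k = 2) and 0.073 (k = 3).

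Accuracy and F1 are correlated, so the three-measure case was simulated, with n = 15 and n = 30 and an exact Wilcoxon test. The ranges cover the correlations above:

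| What counts as significant | Any direction | In the tool's favour |
|---|---|---|
| One t test | 5% | 2.5% |
| Time or one quality measure, t test | 9% to 10% | about 5% |
| Time, accuracy or F1, t test | 11% to 13% | 6% to 7% |
| Time, accuracy or F1, t or Wilcoxon | 13% to 15% | 7% to 8% |

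Most of the rise comes from having several endpoints. Allowing either test on one endpoint lifts 5% only to about 5.5% to 6%.

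**4. A trade of quality for speed.** Suppose time truly improves by 0.8 SD and accuracy truly falls by 0.3 SD. The time test is significant in 82% of trials (n = 15) or 99% (n = 30). The accuracy loss is significant in only 19% or 36%. Most such trials would therefore report a significant time saving and no significant accuracy difference, which is the case Principal Findings reads in the tool's favour.

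**5. Power at .025.** With all 30 coders in one paired test and d = 0.6, power falls from 89% to 82%. With 15 per sequence as the unit and d = 0.8, it falls from 82% to 72%, and 80% then needs 18 per sequence, 36 in total.

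**The case against.** Three objections have force.

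First, Principal Findings is discursive and says what must hold, not what is enough. A reader might infer that the plan passes the tool even when accuracy is significantly worse. The text does not say that. It does not address a significant loss, and because the quality hypothesis is two-sided, such a loss would appear as a main result. Adoption of wrong suggestions is also to be explored. What remains is that the text does not distinguish unchanged from worse, and step 4 shows that a real loss would often not reach significance.

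Second, ranking measures, choosing a test and adjusting for multiplicity often belong in an analysis plan, and one may exist that is not shown. Their absence alone would be no finding. The point stands because this article itself sets .05, counts two tests where its methods produce six p-values, and states an either/or reading.

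Third, the 10% to 15% counts significant results against the tool as well. A reader might take it as the chance of wrongly calling the tool useful, or might treat the six p-values as independent and quote 1 - 0.95^6 = 26.5%. Neither is right. The chance of a false result in the tool's favour is about 5% to 8%, and the t and Wilcoxon tests on the same data are nearly redundant.

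The setting is also modest: a small user study meant to supply baselines, with a pilot planned and a conclusion only about potential. That argues for clarification, not for calling the design invalid.

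**Conclusion.** The point holds in this form. The article permits a usefulness conclusion on either time or quality, runs more tests than the two it counts, names none as deciding and does not control alpha across them. With no true effect, a result in the tool's favour arises in about 5% to 8% of trials against 2.5% for a single test; in either direction, about 10% to 15% against 5%. These rates rest on the assumed correlations and on normal differences, but the first step, from 2.5% to about 5%, follows merely from having two endpoints.

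The article is also silent on a loss in the other endpoint: it does not separate unchanged from worse accuracy, and puts no limit on slightly worse time. This is a gap in interpretation, not an endorsement of harm. Severity: should be fixed.

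**What to change.** Before allocation is unmasked for analysis:

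- Name one quality endpoint (for example F1) and one time endpoint, with one deciding test each. Label the other quality measure and the other test supportive.
- Apply Holm across the two: the smaller p-value against .025 and, if that passes, the other against .05.
- State that the tool is not called useful if the other endpoint is significantly worse. As step 4 shows, this bar alone misses many real losses. So report that endpoint's confidence interval beside any claim of benefit, and describe the result as a trade-off when the interval includes a material loss.
- Correct the count of tests in the Overview, and remove the equivalence label from Table 1 unless a margin is added.

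A formal non-inferiority margin is optional and for the sponsor to set. It can be demanding. With an illustrative F1 margin of 0.05, 30 coders, no true loss and a 95% interval, the requirement is met in 91%, 75%, 42% or 26% of trials for an assumed SD of paired differences of 0.08, 0.10, 0.15 or 0.20. The article gives no SD.

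The cost is the power loss in step 5, which the sample size section should state for whichever unit of analysis applies. Holm loses less than those figures when both effects are real. If 15 per sequence is the unit and 80% power at 0.8 SD is wanted at .025, the target rises from 30 to 36. Otherwise the change is one of wording.

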**Figure 2 figure2:**
[figure not shown]
Statistical power of a 2-tailed t test at the level of 5% depending on sample size per sequence (2-tailed t test with equal SD in both study sequences to compare means).

Based on the plot in Figure 2 derived from power analysis in G*Power [28], we aim to recruit up to 30 participants in total. Multiple methods are used to recruit participants, including contacting hospitals and health authorities directly, announcing at coding seminars and conferences, publishing news in popular science media, and advertising on social media groups and other electronic media.

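### A non-significant usability difference in at most 30 coders cannot rule out usability issues; separately, the Table 1 tests are mislabelled as equivalence tests

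*Protocol article*

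**What the plan says.** **Usability.** Specific Aims lists usability, measured by the system usability scale, as the third of three main end points. Measurements and Analyses says the survey covers the web interfaces with and without Easy-ICD. Evaluation Outcomes expects the system to score above 68 and adds that "we do not expect any significant differences between the usability of the user interfaces with and without our CAC system". Principal Findings then gives the rule for reading the comparison: "if there are no significant differences in usability scores, then usability issues can be ruled out".

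**Time and coding quality.** Measurements and Analyses describes the main analyses as "hypothesis testing using the paired *t* test and Wilcoxon test to compare the before and after means at a significance level of .05". The next sentence reads "Table 1 summarizes these hypotheses based on a test of equivalence". Table 1 gives H0: μ1 = μ2 against H1: μ1 ≠ μ2 for time use and for coding quality. It has no usability hypothesis.

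**Size.** Sample Size Calculation reasons from mean performance in time and from effects in the upper-medium to high range. The caption of Figure 2 is "Statistical power of a 2-tailed t test at the level of 5% depending on sample size per sequence", and from that plot "we aim to recruit up to 30 participants in total".

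**The concern.** There are two separate statements here.

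1. The usability rule treats failure to find a difference as evidence that there is none. The less precise the comparison, the more often the rule returns the reassuring answer. Non-significance is also the result the article expects, so this is the branch most likely to be used. At stake is a published statement that usability played no part, when the data may be compatible with a sizeable deficit.

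2. An equivalence test takes a difference at least as large as a margin as its null hypothesis, and needs that margin. Table 1 has the null of no difference and no margin. The label therefore describes a different test from the one specified.

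**Working it through.** **1. The plan's own figure.** The effect sizes and target power behind 30 participants stand only in Figure 2, which is not shown, so 30 cannot be strictly reproduced. It fits an assumed standardised effect of 0.8 at 80% power: 15 for one paired test, doubled for two sequences as the article describes, 15 × 2 = 30. Nothing below says this figure is wrong. It concerns time, not usability.

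**2. Inputs for the usability comparison.**
- From the article: two-sided 5% level; at most 30 coders; benchmark 68.
- Assumed: all 30 coders give a score for both interfaces; SD of the paired difference of 10, 12, 15 or 20 points; true difference δ of 5 or 10 points.

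**3. Precision.** The 95% CI half-width is t(0.975; 29) × SD / √30 = 2.045 × SD / 5.477 = 0.373 × SD.

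**4. Chance of a non-significant result when a difference exists.** With noncentrality λ = (δ / SD) × √30, this is the probability that a noncentral t with 29 degrees of freedom lies between −2.045 and 2.045. For δ = 5 and SD = 15, λ = 0.333 × 5.477 = 1.83 and the probability is 58%.

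| SD of paired difference | 95% CI half-width | Non-significant, δ = 5 | Non-significant, δ = 10 |
|---|---|---|---|
| 10 | 3.7 | 25% | 0% |
| 12 | 4.5 | 40% | 1% |
| 15 | 5.6 | 58% | 6% |
| 20 | 7.5 | 74% | 25% |

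Without choosing an SD in points: a true difference of 0.3 SD is non-significant 64% of the time, and the smallest difference detectable with 80% power is 0.53 SD. Fewer than 30 complete pairs would make these figures worse.

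**5. Both interfaces poor.** If the two interfaces have the same true mean, the test is non-significant 95% of the time, whatever that mean is. Two interfaces both below 68 would usually pass the rule.

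**6. What a formal equivalence claim would need.** Take a margin of ±5 points for illustration only, a true difference of zero and 30 pairs. The 90% CI lies inside the margin in 70% (SD 10), 44% (SD 12), 14% (SD 15) or 0.5% (SD 20) of trials. With a 95% CI the chances are lower still.

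**7. The label.** Set side by side, the name in the text implies a null of non-equivalence with a margin. Table 1, the paired t and Wilcoxon tests at .05 and the 2-tailed power plot all describe a two-sided difference test. No margin or CI rule appears in the article. The operative specification is clear, and only the name is wrong.

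**The case against.** **The usability sentence does not drive the trial.** The Results overview bases the conclusion on the two tests of time use and coding quality, and Principal Findings names those as the two primary areas of interpretation. This stands, and it sets the severity.

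**The sentence may mean less than it says.** It can be read as discounting usability only as an explanation of performance differences. The text states no such limit, and a non-significant result in 30 coders or fewer would not support that narrower claim either.

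**The benchmark of 68 is in the article.** Evaluation Outcomes expects the system to exceed it, and the end of Principal Findings expects a normal score for the standard interface if Easy-ICD scores significantly better. Neither is joined to the no-difference branch, so the gap is only partly covered.

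**The percentages rest on assumptions.** True. Pairing is itself inferred: the numbered study steps have participants complete the scale at the end, while Measurements and Analyses says it covers both interfaces. The choice of 5 points matters as well, since a 10-point difference would rarely be missed unless the SD is near 20.

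**A stronger reading to avoid.** From the equivalence label a reader might infer that null results for time or quality will be reported as equivalence. The article does not do this. If accuracy does not improve significantly, it turns to time; if neither improves, it speaks of improving the system. A null result is not counted in the tool's favour.

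**Conclusion.** Both statements are wrong as written, and they are separate.

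The usability rule is an invalid inference about one of the three main end points. Under the stated assumptions (30 pairs, SD of the difference 10 to 20 points), it would dismiss a true 5-point difference in 25% to 74% of trials and a true 10-point difference in 0% to 25%. It also cannot detect that both interfaces fall short of 68. The logical fault does not depend on these assumptions; only its size does.

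The equivalence label is a naming error confined to the time and coding-quality hypotheses. It changes no analysis, and the article does not support extending the criticism to the primary tests or to the conclusion drawn from them. Severity for both: should-fix.

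**What to change.** **Usability (Principal Findings).** Remove the statement that usability issues can be ruled out. Report the difference between interfaces with its 95% CI, and each interface's score with a CI against the benchmark of 68 already given in Evaluation Outcomes. Describe a non-significant difference as inconclusive unless the CI excludes differences that the sponsor has declared important before seeing the data. No particular margin is prescribed here.

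**Label (Measurements and Analyses).** Delete the reference to a test of equivalence and call the Table 1 hypotheses two-sided difference tests.

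**Cost.** The changes are wording, a few intervals and, if a claim of no important difference is wanted, one decision by the sponsor in advance. Design, sample size and primary tests stay as they are. The downside is that under a tight margin such as ±5 points the usability comparison will probably be inconclusive, unless the SD is near the low end of the assumed range.
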